### ***The source data***

The source data for the events are print-outs from the electronic medical record of each patient. Furthermore, documents from “The West-Danish heart database” or “The East-Danish Heart database”. Data documentation in Spain and Serbia are prints of the electronic or paper medical record of each patient.

- **Primary endpoints are defined according to the following standard operating procedures:**

### **Death:**

*Validation categories:* Cardiac Death or Non-cardiac death

[figure not shown]

Modified from the "Updated standardized endpoint definitions for transcatheter aortic valve implantation: the Valve Academic Research Consortium-2 consensus document. European Heart Journal (2012) 33, 2401-2418

### **Heart failure**

*Validation categories:* HHF; Non-HHF

- During index admission, New admission or unscheduled outpatient clinic visit \*\*
- Symptoms, signs and results of diagnostic test need to be assessed by a medical doctor.

[figure not shown]

\*According to ESC guidelines for diagnose and treatment of acute and chronic heart failure 2012. European Heart Journal (2012) 33, 1787-1847 and “2014ACC/AHA Key Data Elements and Definitions for Cardiovascular Endpoint Events in Clinical Trial”. Circulation.2015;132:302-361

Please note:

- Patients with cardiogenic shock will fulfil the definition of heart failure.
- That acute heart failure developed prior to randomisation should not be considered an event. Neither chronic heart failure diagnosed prior to randomisation.
- That initiation or increment of these drugs due to hypertension is NOT an event. The independent end-point committee will subsequently confirm the diagnosis.

Encounter type:

**In-hospital:** An event where the patient is admitted to the hospital with a primary diagnosis of HF where the length of stay is at least 24 h (or extends over a calendar date if the hospital admission and discharge times are unavailable), where the patient exhibits new or worsening symptoms of HF on presentation, has objective evidence of new or worsening HF, and receives initiation or intensification of treatment specifically for HF.

**Unscheduled outpatient clinic:** An event where the patient has an urgent, unscheduled office/practice/ED visit for a primary diagnosis of HF but is not admitted to the hospital, where the patient exhibits new or worsening symptoms of HF on presentation, has objective evidence of new or worsening HF, and receives initiation intensification of treatment specifically for HF, with the exception that changes to oral diuretic therapy do not qualify as initiation or intensification of or treatment.

- **Secondary endpoints are defined according to the following standard operating procedures:**

For the secondary endpoint, we are interested in those MIs occurring outside the setting of any future elective PCI procedure.

**SOP for Diagnostic and clinical indications of MI \*, More than 48 hours after index pPCI**  
**Event report in Condi 2**

*Validation categories:* MI ; No MI

[figure not shown]

\*Modified from: "Third universal classification of myocardial infarction". European Heart Journal (2012) 33, 2251-2567 and "2014 ACC/AHA Key Data Elements and Definitions for Cardiovascular Endpoint Events in Clinical Trial". Circulation.2015;132:302-361

**SOP for Stroke Event report in Condi 2**

*Validation categories:* Definite ischaemic stroke; Haemorrhagic stroke; Transient ischaemic attack; No evidence of stroke

[figure not shown]

\*According to “2014ACC/AHA Key Data Elements and Definitions for Cardiovascular Endpoint Events in Clinical Trial”. Circulation.2015;132:302-361

### Evaluation of the electrocardiogram:

[figure not shown]

### SOP for clinical indicated coronary REVASCULARISATION (not scheduled at index event) report in Condi 2:

Validation categories: Yes or No

[figure not shown]

\*Modified from: "Third universal classification of myocardial infarction". European Heart Journal (2012) 33, 2251-2567 and "2014ACC/AHA Key Data Elements and Definitions for Cardiovascular Endpoint Events in Clinical Trial". Circulation.2015;132:302-361

**SOP for Procedure-related AMI report in Condi 2 (not part of secondary outcome measures)**

Validation categories: Yes or No

[figure not shown]

\*Modified from: "Third universal classification of myocardial infarction". European Heart Journal (2012) 33, 2251-2567 and "2014ACC/AHA Key Data Elements and Definitions for Cardiovascular Endpoint Events in Clinical Trial". Circulation.2015;132:302-361

- **S/T methodology and associated work plan**

- **Trial Design:**

Multinational investigator-driven, multi-centre, randomised, controlled, single-blind (Outcomes Assessor), parallel assignment, prospective clinical efficacy trial to investigate whether RIC can improve clinical outcomes (cardiac mortality and HHF) at one year in STEMI patients undergoing pPCI.

- **Setting**

In all 5700, STEMI patients will be included.

Four centres with on-site facilities for pPCI in Denmark will recruit app. 1,800 STEMI patients in total over a 36-month period.

Centres in Asturias, Spain, and Belgrade, Serbia will recruit app. 800 STEMI patients in total over a 36-month period.

An aligned sister study in the ERICCA-collaboration (ERIC-pPCI) including 30 primary PCI centres in the UK will include 3,000 patients.

Data collection and analysis will be undertaken through the Department of Cardiology and Department of Clinical Epidemiology, Aarhus University Hospital Skejby Clinical Trials Unit.

- **Target population**

Possible study candidates are patients with putative STEMI acute admitted to one of the heart centres. There will be no advertising for patients. A total of 5,700 patients are to be included over a 36 months period.

| Inclusion criteria for recruitment                                                                                                                                                        | Exclusion criteria for recruitment        |
|--------------------------------------------------------------------------------------------------------------------------------------------------------------------------------------------------|--------------------------------------------------|
| Male and female patients (>18 years old) presenting with chest pain for more than 30 minutes                                                                                                     | Previous by-pass surgery                         |
| Putative STEMI (ST-elevation at the J-point in two contiguous leads with the cut-off points: $\geq 0.2$ mV in men or $\geq 0.15$ mV in women in leads V2-V3 and/or $\geq 0.1$ mV in other leads) | MI or treatment with thrombolysis within 30 days |
| Informed consent obtained                                                                                                                                                                        | New left bundle branch block                     |
| Life expectancy of more than 1 year                                                                                                                                                              | Patients treated with cooling                    |
|                                                                                                                                                                                                  | Paresis of upper limb                            |
|                                                                                                                                                                                                  | A-V-shunt                                        |

- **Study progress**

- **Patient information**

The patient will be informed and treated according to the national and international guidelines for Good Clinical Practice and protected under the Act concerning the processing of personal data and health law.

The intervention is performed in the acute phase. Consequently, in addition to the ordinary written patient information (A) a short written information (B) is given in the ambulance (one A4 sheet). Because the nature of the disease and the intervention are acute, the usual requirements about a 24-hour time for consideration and discussion with a lay representative cannot be met. The inherent acute nature of the study necessitates circumvention of these usual requirements as it has previously been done in comparable acute studies. This approach is reasonable because the intervention is without any known risk and because the intervention has potential benefit for the individual patient.

The admitting ambulance doctor, the doctor at the receiving hospital, or the paramedic will orally inform the patient based on the short written information (B) and hand out the written informations (A+B). After oral and written informed consents are obtained the patient will sign the agreement form and be randomised via a secure web site to pPCI with or without RIC by the doctor on duty at one of the receiving hospitals. Computer-generated blocked randomisation lists, stratified by centre, will be prepared in advance of the study.

After information is given in the acute phase, the patient does not have much time for reflection before signing the informed consent form. Therefore, a study nurse will give the patient additional oral information after the acute phase by or the doctor performing the pPCI based on the full written information (A). Both during the first and second stage of information it will be emphasised that the patient has the right to withdraw his/her informed consent at any time.

- **Procedures and treatment**

*Control group:* Will be treated according to standard procedures in the ambulance.

*Intervention group, RIC group:* The CellAegis auto RIC (automated blood pressure cuff) will be placed on the upper arm and inflated to 200mmHg for 5 minutes and then deflated for 5 minutes, a programmed cycle which is repeated 4 times in total (therefore the total length of the RIC protocol is 40 minutes). If the initial systolic blood pressure is >175mmHg, a manual cuff will be used to and inflated to 25mmHg above the systolic blood pressure. In recruiting centres where randomisation occurs at the hospital or in cases with short transportation time, the RIC protocol will continue during PCI until successful or until immediately before reperfusion.

Further, the patients will be treated according to standard procedures in the ambulance.

|                                                    | Acute intervention |         | Index event    | Follow up |
|----------------------------------------------------|--------------------|---------|----------------|-----------|
| Randomisation                                      | Intervention       | Control |                |           |
| Blood samples                          |                    |         | X              |           |
| e-CRF                                  |                    |         | X              | X         |
| Echocardiography                       |                    |         | X              | X         |
| Electrocardiography                    | X                  |         | X  |           |
| Quality of life
(EuroQol EQ-5D-5L)  | X                  |         |                | X         |

 Blood samples for Ck and TnT drawn acute, 6-8 ( $\pm$ 4), 24 ( $\pm$ 8) and 48-72 (+6) hours post-PCI. Samples will be analyzed immediately.

 Research assistant complete the electronic case record form. Information regarding re-hospitalisation or death will be drawn from (electronic) patient chart.

 Echocardiography (sonogram of the heart, performed at day one to three and three to six months after-pPCI)

 Electrocardiography will be measure acute (admitting ECG), just prior to pPCI and 90 minutes post-PCI

 Quality of life (EuroQol EQ-5D-5L) at 6-8 weeks and 12 months via printed copy or via internet based questionnaire.

pPCI incl. the use of stents and antithrombotic regimens will be performed according to standard procedures at the treating hospital.

Blood samples will be drawn according to standard routine; no extra biomarkers will be measured. An extra sample of 15 ml will be drawn 72 H post pPCI. All blood samples will be analysed immediately. We will not establish a bio bank.

In Denmark, we will draw information regarding re-hospitalisation for hearth failure, AMI, revascularisation, or death from the (electronic) patient chart.

The Quality of life questionnaire (EuroQol EQ-5D-5L) will be performed as a sub-study on app. 400 patients. The patients will after the acute pPCI treatment be asked for the capacity to fill in the questionnaire via a printed copy or via a secured individual internet based access.

#### ○ **Discontinuation of study participation**

On request, a patient can withdraw from the study at any time, or when medically necessary, as judged by the Investigator. If a patient does not return for a scheduled visit, every effort should be made to contact the patient. In any circumstance, every effort should be made to document patient outcome if possible.

If a patient decides to withdraw from the study, he/she will be contacted in order to, if the patient agrees, obtain information about the reason(s) for discontinuation and any experienced adverse effect. The date and reason for the withdrawal will be recorded in the case record form.

- **Benefit of the study**

*Potential benefits:* Participating patients will be offered a clinical outpatient control, incl. echocardiography, three months after pPCI.

*Disadvantage:* In relation to the inflation of the blood pressure cuff temporary moderate pain in the treated arm might occur. Otherwise, RIC has previously been proven to be without side effects.

An extra blood sampling of app. 15 ml will be drawn 72 hours after pPCI. A small but insignificant risk of local infection in relation to this is a risk.

- **Statistics**

- **Power Calculations**

Primary combined clinical endpoint

The primary combined endpoint will be cardiac death and HHF at 12 months in all-comer STEMI patients. Importantly, the CONDI-2 trial will also be adequately powered to detect an effect of RIC on clinical outcomes in the higher-risk proximal LAD STEMI patient subgroup. The reason for this is that previous clinical trials have suggested that the STEMI patients most likely to benefit from a cardioprotective intervention administered as an adjunct to pPCI, are those presenting with a proximal LAD STEMI. These endpoints have been selected as they are the most relevant clinical endpoints on which RIC, an intervention which protects cardiomyocytes against acute IRI, is most likely to impact on. According to the UK NIAP 2008 database, cardiac mortality at 12 months ranged from 5.8%-16.7% depending on the call to balloon time, with the overall 12 month death rate of 8.7% for all pPCI patients. Results from our own institution have revealed a 1-year total mortality of 9.4% and a cumulative risk of readmission with HF of 8% (1). In another clinical study, the incidence of HHF was 12.7% at 12 months post-pPCI (18). The previous clinical data include all patients presenting with a STEMI. We have based our power calculations on these published series, accounting for the marked improvements in clinical outcomes in the contemporary era by using much more conservative event rates.

All STEMI patients: As a conservative estimate we will use a combined cardiac death and HHF event rate of 8% at 12 months for all-comer STEMI patients. In the CONDI-2 study we estimate the effect size to be a 25% relative reduction in the event rate. The rationale for this is based on the reductions in MI size observed in proof-of-concept clinical studies in which RIC and related therapeutic interventions such as ischemic postconditioning which have reported 40-50% reductions in MI size. To demonstrate a 25% reduction in the primary composite endpoint in the RIC-treated group (from 8.0% to 6%), with 80% power and at the 5% significance level, would require 2553 patients per treatment arm which equates to 5106 patients in total. Therefore, we will need to recruit 5,700 all-comer STEMI patients (allowing for a 10% drop-out rate at 12 months) between UK and Denmark (2,600 STEMI patients in the Denmark, Serbia and Spain and 3,000 STEMI patients in UK).

**Summary of Changes in the CONDI-2 protocol**

Proximal LAD STEMI: Patients presenting with the larger proximal LAD STEMI have worse clinical endpoints. In the AMISTAD II study (2,118 patients), which investigated the effect of adenosine as an adjunct to pPCI, only recruited LAD STEMI patients, and in these patients the 6-month primary combined endpoint was 19.6% (11.3% cardiac death, 8.3% HHF) (18). As a conservative estimate we will use a combined cardiac death and HHF event rate of 15% at 12 months for proximal LAD STEMI patients. To demonstrate a 30% reduction in the primary composite endpoint in the RIC-treated group (from 15.0% to 10.5%), with 80% power and at the 5% significance level, would require 862 patients per treatment arm which equates to 1,724 patients in total (862 proximal LAD STEMI patients each in the UK and Denmark). Therefore, assuming that about 45-50% of all STEMI patients present with a proximal LAD STEMI, in order to recruit 1,724 proximal LAD STEMI patients, we will need to recruit about 4,300 all STEMI patients (allowing for a 5% drop-out rate at 12 months) between UK, Serbia, Spain, and Denmark.

- **Interim analyses**

We will perform an interim analysis for evaluation of the actual event rate after inclusion of 50% of the patients. If this shows lower event rate than expected, a new sample size calculation will be performed. Furthermore, we will perform an independent safety analysis after inclusion of 50% of the patients.

- **Pre-specified subgroup analyses**

We will undertake a limited number of subgroup analyses: age, gender, diabetes, duration from symptom onset to pPCI, and duration from end of RIC to pPCI. These subgroups will be analysed using interaction tests. These factors may influence the response to cardio-protective strategies such as RIC and pharmacological agents.

- **Statistical analysis**

We will produce a detailed statistical analysis plan prior to un-blinding of any data. The primary analysis will be a comparison of the event rate one year after STEMI between RIC and control arms of the trial. We will use survival analyses for cardiac mortality, HHF, and other clinical endpoints. Further, we will use area under the curve to assess the MI size. All patients will be included in the data analysis after the intention-to-treat principle.

- **Project timetables and recruitment feasibility**

The total duration of the study will be 56 months:

- 1) 0-6 months: Study preparation
- 2) 6- 48 months: Patient recruitment
- 3) 56-62 months: Study analysis. In order to recruit 5,700 STEMI patients over 42 months, 136 patients are to be included per months. Each of the recruiting centres provides 24 hours a

day, 7 days a week pPCI service. The on-call cardiologists will recruit during office hours and out of office hours allowing non-stop recruitment.

- **Study status**

Until now, (medio January 2017), 1,823 patients are included in the study. Of which 1,382 are included in Denmark, 152 in Belgrade and 289 in Spain. Furthermore more 1,320 patients are enrolled in the ERIC-pPCI

- **Ethical issues**

The regional ethics committee before initiation of the study (No. 1-10-72-167-13) approves the study protocol. The study is registered at the Danish Data Protection Agency.

Furthermore, the local regional ethics committees in Asturias, Spain, and in Belgrade and Novi Sad, Serbia have approved the study and awaits final approval in the UK.

The clinical trial is registered on [www.clinicaltrials.gov](http://www.clinicaltrials.gov) (NCT01857414). Good clinical practice will be observed through the trial and we will respect the appropriate international, European and national legislation and guidelines.

The Data Monitoring Committee will monitor the study. Study investigators must report all unexpected events, independently of seriousness (adverse event (AE), serious adverse event (SAE)) to the safety group of the study. The study is not a pharmaceutical drug trial or a testing of new medical devices and therefore none of the reported events is to be considered as side effects (adverse reaction (AR) or serious adverse reactions (SAR)).

The nominated sponsor of our research study will be University of Aarhus.

The study participants are during study covered under the law on patient insurance.

- **Data storing**

All study data are stored in an electronic CRF, where data are blinded and patients can be identified via a study identification number, only. In the medical record of the patient participation in the study will be recorded.

Data will be stored at the dept. of Cardiology, Aarhus University Hospital, Skejby for 15 years and subsequently the documents will be shredded.

- **Expected impacts listed in the work program**

RIC is low-cost intervention, which can be easily implemented as part of routine clinical care of STEMI patients undergoing pPCI. If successful, this project will be expected to improve clinical outcomes for STEMI patients by reducing the number of cardiac deaths and reducing the number of patients HHF at one year.

Positive as well as negative and inconclusive results will be widely disseminated through national and international scientific journals and conferences.

The authorship order: [name] representing the ERRICA cooperation in the UK will be first author and professor [name], Dk will be last author. The following authorships will be given according to numbers of patients included per site. There must be included 100 patients to have one authorship and 250 patients to obtain the second authorship. However, all principal investigators will be offered authorship. From Spain, this includes: MD [name] [name] and MD [name]. From Serbia, [name], [name], and MD [name]. From Denmark MD [name] and [name]. From UK: In the UK, PIs from the top 10 recruiting sites will be invited to be co-author on main paper – in addition [name] (clinical fellow), [name] (senior statistician), [name] (trial statistician), [name] (Trials Manager), [name] (Database manager), [name] (senior trials manager).

All Danish/Spanish/Serbian PCI operators and committee members to be listed as collaborators (PubMed listed).

The order of appearance of the scientific authors will be according to the included number of patients at the centre. This will secure inclusion on PubMed and other medical scientific databases.

The centres involved in recruiting the patients will not be involved in any competing studies, thereby maximising the feasibility of recruitment.

- **Financial standing**

The study is supported by: The Danish Council for Strategic Research with DKK. 19.6 kr. mill, The Danish Council for Independent Research, Medical Sciences with DKK. 3.6 mill, and The Novo Nordic Foundation 600.000 DKK. The Lundbeck Foundation with DKK 4.6 mill. The money is deposited on a bank account subjected to public current audit. None of the in the study implicated doctors or nurses have any financial benefit of the study.

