### 39.2. Expected adverse events (recognised to be caused by the RIC stimulus)

The benign nature of the RIC stimulus excludes there being any expected serious adverse events. The following are expected non-serious events in response to the RIC stimulus and will be recorded on the Case Report Form. They do not need to be reported to the Clinical Trials Unit.

2. Skin petechiae caused by cuff inflation

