#### 39.6.2. Assessment of causality

Probable: A causal relationship is clinically / biologically highly plausible and there is a plausible time sequence between onset of the adverse event and the RIC procedure.

Possible: A causal relationship is clinically / biologically plausible and there is a plausible time sequence between onset of the adverse event and the RIC procedure.

Unlikely: A causal relationship is improbable and another documented cause of the adverse event is most plausible.

Unrelated: A causal relationship can definitely be excluded and another documented cause of the adverse event is most plausible.

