| 
Name of Investigational Medical Device: The CellAegis automated cuff
                                                                                                                                                                                                                                                                                                                                                                                                                                                                                                                                                                                                                                                                                                                                                                                                                                                                                                                                                                                                                                                                                                                                                                                                                                                                                                                                           |

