Both pre-clinical and recent clinical studies have demonstrated that treatment strategies such as Remote Ischaemic Conditioning (RIC) applied at the time of myocardial reperfusion can reduce myocardial infarct size, confirming the existence of myocardial reperfusion injury (6). In this respect, RIC has been shown to limit myocardial infarct size and preserve cardiac function in recent proof-of-concept clinical studies in STEMI patients undergoing pPCI (8;9). Cardioprotection by RIC is most commonly achieved by manual or automatic inflation of a blood pressure cuff to induce four 5-minute cycles of limb ischaemia and reperfusion (10;11), a technique that was first pioneered by our network allies at Aarhus University Hospital and University College London (12). Based on these studies, we have demonstrated that RIC applied in the ambulance during transport to the pPCI unit reduced MI size in STEMI patients undergoing pPCI (8). Subsequently, it has been demonstrated that RIC can reduce myocardial injury in patients undergoing coronary artery bypass graft (CABG) surgery (13), in children undergoing corrective cardiac surgery (14) and in patients with stable angina undergoing elective PCI (15).

However, whether this virtually cost-free non-pharmacological and non-invasive therapeutic strategy can actually improve clinical outcomes in STEMI patients has never been investigated in a randomized controlled clinical trial.

- **Hypothesis**

RIC followed by pPCI improves clinical outcomes in STEMI patients when compared to STEMI controls undergoing standard pPCI evaluated one year post PCI.

- **Objectives**

- **Overall primary objective**

- To determine whether RIC improves clinical outcomes (cardiac mortality and hospitalisation (in-hospital or outpatient clinic) for heart failure (HHF)) at one year in STEMI patients undergoing pPCI.

- **Secondary objectives:**

- To determine, in the pre-specified subgroups, whether age, gender, diabetes, and duration of chest pain to PCI influence the response to RIC.
- To determine whether RIC preserves left ventricular function measured by echocardiography after three day and three-six months post pPCI
- To determine whether a correlation between biomarkers, patient susceptibility to ischaemia-reperfusion injury and the treatment strategies of RIC can be found. Measured as area under the curve 72 hours post pPCI
- To trial the CellAegis automated cuff in its largest clinical study to date.

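### CONDI-2 v10 rules in advance that no reported event is an adverse reaction, so no event in its RIC arm can be classed as RIC-related, although the same protocol names an investigational device and foresees cuff pain

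*Supplement*

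**What the plan says.** CONDI-2 v10, 13 Ethical issues, first obliges investigators to report every unexpected event, serious or not, to the study's safety group, with a Data Monitoring Committee overseeing the study. It then states: "The study is not a pharmaceutical drug trial or a testing of new medical devices". From this it concludes that "none of the reported events is to be considered as side effects (adverse reaction (AR) or serious adverse reactions (SAR".

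Elsewhere in the same protocol:

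- The Synopsis has the entry "Name of Investigational Medical Device", completed with the CellAegis automated cuff.
- 5.2 Secondary objectives includes "To trial the CellAegis automated cuff in its largest clinical study to date".
- 9 Benefit of the study says: "In relation to the inflation of the blood pressure cuff temporary moderate pain in the treated arm might occur". The next sentence says RIC is *otherwise* free of side effects, which treats the pain as one.
- 10.2 Interim analyses plans an independent safety analysis after half the patients are included. 8.3 has withdrawing patients asked, if they agree, about adverse effects they experienced.

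ERIC-PPCI v5 handles the same questions differently:

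- 39.2 lists one expected effect of the stimulus, "Skin petechiae caused by cuff inflation", to be recorded on the CRF.
- Under 39.1 and 39.5, an unexpected event that is neither an endpoint nor a listed complication is reported. If non-serious, it is assessed for causality and reported within 14 days.
- Under 39.4, the site principal investigator assesses the causality of each reported SAE, and confirmed unexpected and related SAEs go to the sponsor, the ethics committee and the DSMC. The scale in 39.6.2 has four levels, and the upper two require that "there is a plausible time sequence between onset of the adverse event and the RIC procedure".

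The combined SAP v3 describes no analysis of adverse events.

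**The concern.** Whether cuff inflation caused an event is a question of fact. The regulatory status of the device does not answer it, so the *therefore* in Ethical issues does not follow. The premise also sits badly with a protocol that calls the cuff investigational, sets out to trial it, and foresees pain from it.

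The documents rely on RIC being harmless. CONDI-2 v10 (8.1 Patient information) justifies its shortened acute consent partly by saying the intervention has no known risk, and 13.2 anticipates use in routine care. If CONDI-2 reports no adverse reactions, a reader would take that as evidence of safety. Under the rule it could not have come out otherwise. The two trials would also describe the harm of one stimulus on different bases.

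**Working it through.** **1. The plan's own figures.** SAP v3, Sample Size, uses 8.5% against a 25% relative reduction (0.75 × 8.5% = 6.375%), with 80% power and two-sided 5%. The usual formula is n = [1.96·√(2p̄(1−p̄)) + 0.8416·√(p₁(1−p₁) + p₂(1−p₂))]² / (p₁−p₂)². With p̄ = 0.074375 it gives 2,393 per arm, against 2,395 stated. Then 4,790/0.90 gives 5,323, against 5,400 stated. Both agree closely. The split is 2,600 (CONDI-2) + 2,800 (ERIC-PPCI) = 5,400.

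**2. Whom the rule touches.** CONDI-2 controls receive standard care without a cuff (8.2 Procedures and treatment), so only the RIC arm can have RIC-related harm. Assuming 1:1 allocation, as the equal arm sizes imply:

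- CONDI-2 RIC arm: 2,600/2 = 1,300
- Share of RIC-allocated patients: 1,300/2,700 = 48.1%
- Share of all pooled patients: 1,300/5,400 = 24.1%

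CONDI-2 v10 gives its own combined total as 5,700, with components 2,600 + 3,000 = 5,600. On those, the share of RIC-allocated patients is 1,300/2,850 = 45.6% or 1,300/2,800 = 46.4%. The conclusion does not change.

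**3. The same event in the two trials.** Both deliver four cycles of 5 minutes' inflation and 5 minutes' deflation (CONDI-2 8.2; ERIC-PPCI 35.1).

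| Event under an active cuff | CONDI-2 v10 | ERIC-PPCI v5 |
|---|---|---|
| Unexpected serious limb event | Reported as an SAE; may not be called a reaction | Reported as an SAE; causality graded; to the DSMC if confirmed as related |
| Arm pain | Foreseen, so not clearly within a duty limited to *unexpected* events; no other routine collection named | Not on the expected list, so an unexpected non-serious event, graded, due within 14 days |
| Petechiae | Not mentioned | Expected; recorded on the CRF |

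**4. What a count by arm can still show.** The documents give no background rate for reported events, so I assume 1%, 2% and 5% in controls. With 1,300 per arm, 80% power, two-sided 5%, no losses and the formula in step 1, the smallest detectable RIC-arm rates are about 2.4%, 3.9% and 7.7%. The comparison by arm is informative, but mainly for sizeable excesses. It cannot recover pain that was not recorded.

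**5. How far an amendment reaches.** CONDI-2 v10, Study status, reports 1,823 of its patients included by mid-January 2017. That leaves 2,600 − 1,823 = 777, or about 389 on RIC. Grading only from then on would cover at most 389/1,300 = 30% of the CONDI-2 RIC arm.

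**The case against.** The strongest reply is that the sentence bars a label and does not stop collection. Unexpected AEs and SAEs are reported, a committee monitors them, and a safety analysis is planned at 50% inclusion. Comparing events by randomised arm is in any case sounder than case-by-case attribution, especially in a trial without a sham. This stands, and it limits the point to attribution and to foreseen effects. It does not repair the rule: the content of the safety analysis is not described, and foreseen pain may never enter the data.

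Several stronger readings are tempting and should be resisted:

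- A reader might infer that RIC-related harm in CONDI-2 can never be counted. Unexpected events can be, by arm.
- A reader might infer that sites must file such events as unrelated. CONDI-2 v10 has no such category, and declining to call an event a reaction is not the same as grading it unrelated.
- A reader might take the premise to be that no device is tested. The text says no *new* device, which leaves room for an existing one. The tension with the word investigational remains, but it is softer.
- A reader might apply 48% to all pooled patients. That would count controls who never wear a cuff.
- A reader might call arm pain the commonest harm. No frequency is given, and the text says only that it might occur.
- A reader might compare an upper confidence limit from the ERIC-PPCI RIC arm alone with one from both RIC arms. That treats CONDI-2 as giving no information, although absence of reported unexpected serious events would itself bound the related ones. It also ignores the patients already enrolled.

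Finally, SAP v3 plans no pooled safety analysis, so none is broken. It refers to separate SAPs for each trial and to a parallel document on the variables to be combined. Those are not shown, and safety may be handled there.

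**Conclusion.** The point holds in a limited form. CONDI-2 v10 contains an explicit, current rule that settles causality before any event is seen, and it conflicts with three other places in the same protocol. As a result, no event among about 1,300 RIC-allocated CONDI-2 patients (48% of the pooled RIC arm, 24% of all pooled patients) can be classed as RIC-related, while ERIC-PPCI grades causality. A finding of zero adverse reactions in CONDI-2 would be a consequence of the definition. Separately, arm pain falls into a gap in CONDI-2 and is an unexpected event in ERIC-PPCI.

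The sizes assume 1:1 allocation and the SAP v3 recruitment split. The primary efficacy analysis is unaffected. The sponsor should correct this because it bears on what may be claimed about safety.

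**What to change.** 1. Delete the conclusion in CONDI-2, Ethical issues, that no reported event is an adverse reaction, and reconcile that section with the Synopsis, 5.2 and 9.
2. From the amendment onward, have CONDI-2 investigators grade each reported event on the scale in ERIC-PPCI 39.6.2, and send related SAEs to the CONDI-2 Data Monitoring Committee.
3. Use one list of foreseen cuff effects (petechiae and arm pain) in both protocols, recorded on each trial's CRF or e-CRF.
4. Present events by randomised arm, without attribution, beside the graded results.

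The cost is a CONDI-2 amendment with one causality field and two tick boxes on the e-CRF, and a matching change to the ERIC-PPCI expected list and CRF for arm pain. There are two limits. Patients already enrolled are covered only if their events are graded retrospectively, which is extra work. And because CONDI-2 has no sham, site grades may be coloured by known allocation, which is why step 4 is needed.
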